### Study procedures

2.5

Specifically, the trial will be executed in four steps:1.Education and outreach

Hunters will be invited to participate in this study through clubs and professional organizations as well as through social media. There will be a documentary-style video trailer used as an outreach tool. An overview of the rationale for the trial as well as the study protocol will be shared at each of the club meetings. Business-card-size information resources will be handed out with contact and background information (Fig. 4). Additionally, the link to the online video describing the study will be emailed to hunters through the clubs.

**Fig. 4 fig4:**
[figure not shown]
**Resource created for hunters interested in participating in the study.** For outreach and to facilitate participant recruitment, bi-fold business-card sized information sheets that can be kept with the potential participant's firearms license are being created. The front and the back of the resource is shown.

It will be explained to hunters that after they shoot an animal that they must take a photograph of the animal to document shot placement. The photograph will be at least 72dpi resolution and clearly identify the location the animal was shot. The hunters must provide the weight of their bullet (brand if possible) and number of shots used to harvest the animal. This step is important to verify shot placement, and also to confirm the ability of the prospective participant to follow the directions for the study. The pictures indicating shot placement will be emailed to [contact] with the hunter contact information and a time available for a phone call. All hunters that send pictures will receive a phone call from the study coordinator.2.Consent to enrol in study

Hunters that successfully email photographs of the harvested animals with the required information will be interviewed by the study coordinator for enrollment in the study. Enrollment in the study will occur in two steps. First, a telephone call will explain to the participant the consent form (see supplemental data) and answer questions the participant has regarding the study. The participant will be asked approximately how many times per week they eat lead-shot animals and if they are willing to abstain from eating lead-shot meat for 9, 18, or 27 days. Second, if the participant is still interested in participating, a consent form will be mailed to the participant and a time will be scheduled for a subsequent telephone call to allow formal consenting of the participant. Preliminary discussions with hunters have determined that a majority would be willing to abstain from eating wild-shot meat for one month for the study. However, if hunters decline to participate based on the length of abstaining from eating wild meat, they will be offered to still participate and abstain from eating lead-shot meat for 9 days (or the maximum they are willing to abstain). The consent form package will include a postage-paid envelope.

Formal consenting for the trial will occur via telephone and the study coordinator will work through the form with the participant. Once the pages have all been reviewed the participant will sign the consent form and return the form by mail.3.Collection of study data

Hunters will be instructed to prepare their game in the usual manner. Typically, this involves mincing meat from the front legs of the animals and processing the rear quarters of the animal into larger cuts of meat. The participants will be instructed to text the study coordinator when processing occurs and the study coordinator will confirm receipt of the text message.

Prior to the first meat being eaten from the lead-shot animal, a baseline blood lead level will be measured. When a meal is eaten from the harvested game that involves ≥85 g (∼3/4 cup) of minced meat per person, the participants will be instructed to text the approximate number of servings eaten and notify the study coordinator of having eaten the meal. Between 2 and 4 days after eating the meal, the participant will report to the clinical laboratory in their local area for blood draw and complete blood count measurement. Each day that the participants are eligible for a blood draw they will receive texts from the study coordinator. After completing the blood draw, the participants will text the study coordinator.

Once the data from the clinical laboratory have been collected the participants will be contacted by the study coordinator. The participants will be instructed to report to the clinical laboratory at 9, 18 and 27 days during the abstention period for blood lead measures. Participants will receive a weekly text to remind them about the study. At the clinical laboratory, participants will provide a blood sample and the clinical laboratory will measure lead blood levels and complete blood count according to the standard clinical protocol. These values will be reported to the study coordinator. The study coordinator will maintain records of the results as described in Data Handling and Record Keeping.

During the study the participants will be requested to provide information on any activities that week that may have exposed them to lead such as reloading ammunition or any of the study exclusion criteria.

No biological samples will be retained.4.Analyses and reporting of results

All data will be collected prospectively by the study coordinator and stored in a password-protected Excel spreadsheet for analysis. The data will be provided blinded to the Principal Investigator for analyses as described in the statistical methods section.

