This current study establishes the parameters necessary to assess whether hunters eating meat shot with lead projectiles have elevated blood lead levels. For this feasibility study, hunters will be asked to abstain from consuming meat harvested with lead projectiles for 7 days. After 7 days, hunters will provide a baseline blood sample. Hunters will then consume meat that was harvested with lead projectiles and provide an additional blood sample 2–4 days (the blood-lead level peak post exposure [17]) after consumption. Hunters will also provide subsequent blood samples at periods of 9, 18, and 27 days. During the 27 day period, hunters will not consume meat harvested with lead projectiles. (Fig. 1). We have chosen to use deer as the species for this study to reduce variation; New Zealand is the ideal place to conduct this study because of year-round hunting of deer [18]. This study design will allow for the development of a conditional linear effects model, which will account for the inherent correlation of longitudinal data that involves repeated measures on the same subject over a period of time. A conditional model will also be more robust to any missing data that may arise through the course of the study, which may also facilitate a reduction in the required number of subjects necessary for this feasibility study.

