**Fig. 1 fig1:**
[figure not shown]
**Design of the current feasibility study**. Participants in the current study will harvest deer with standard lead projectiles. A baseline lead measure, a measure immediately after eating the lead-shot meat, and measures at 9, 18 and 27 days. These blood lead levels will allow a model to be built determining appropriate sample size for each potential washout period.

If this current observational study determines that an interventional study is feasible, the subsequent interventional study would randomize hunters into two groups: hunters using lead projectiles and hunters using non-lead projectiles. All hunters would undergo an initial wash-out period and then have baseline blood lead level recorded. Hunters in both cohorts would then eat the harvested meat and blood lead levels would be recorded 2–4 days after eating the self-harvested meat. Hunters would then repeat this process for a replication of 3 times during the year. After one year, the hunter would cross over to the other type of projectile and repeat the entire process again (Fig. 2). This case crossover study would be analyzed utilizing a conditional linear effects model to account for the correlative nature of longitudinal data involving repeated measures. Additionally, this model will allow for other factors to be included in the model, including time-dependent covariates. Additionally it would be possible to use isotope analysis to identify if the lead levels in the blood of participants were primarily from the environment or from the lead projectiles [10], [19]. Fortunately, baseline blood lead levels in New Zealand are similar to levels in other developed countries [20] thus allowing a broad extrapolation of the data generated.

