### Primary outcome and sample size determination for the feasibility study

2.6

A two-tailed dependent *t*-test was utilized to perform a power analysis and determine sample size necessary for the study. A dependent *t*-test was used for the power analysis in order to ensure sample size would not be underestimated. To address correlation and the nature of longitudinal data, a conditional linear effects model will then be utilized to determine differences in the pattern of mean blood lead level over time. A sample size calculation was performed (SigmaPlot 12.5; Systat) and the following values were assigned based on previous literature and clinical logic: Expected Difference in Means: 0.074; Expected Standard Deviation: 0.19; Number of groups: 2; Desired Power: 0.8; Alpha: 0.05. The expected mean difference is derived from preclinical data [17] and 7 day washout. This calculation resulted in a sample size calculation of 54 data points in each abstention cohort.

We expect 25% attrition from the study and therefore we will be required to recruit a total of 68 participants.

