### Statistical methods and analysis of feasibility study

2.7

All data will be summarized using descriptive statistics (i.e. mean ± SEM). Data will be tested for normal distribution using a QQ plot and the Shapiro-Wilk test. Visualization and assessment of normality will be achieved through creation of histograms and boxplots. The primary dependent variable is mean blood lead level. In order to determine whether there is a difference in the pattern of mean blood lead level over time while accounting for lead exposure, mean blood lead level at baseline, 2–4 days, 9 days, 18 days and 27 days will be analysed using a conditional model that will account for the correlative nature of longitudinal data involving repeated measures taken from the same subject. This model is advantageous for a variety of reasons, including that this approach can handle unbalanced data (missing data at various time points), as well as continuous and discrete predictors. This model will also be able to model covariance structure which is important when handling correlated data. A random intercept will be utilized to account for natural variation in baseline blood lead measurements among hunters. Predictors will include the grouping variable of lead vs. lead-free projectile, time and the interaction of group and time. The interaction term will allow the investigators to identify whether blood lead level changes over time, thereby determining the most appropriate wash-out period. Other factors, such as any exposure to lead ammunition and isotope analysis may be included as factors in the analysis.

Categorical variables will be analyzed using chi-square tests. Variables including (agree to participate in study/decline to participate because of request to abstain/not because of request to abstain) will be used to determine the feasible length of abstaining from eating wild-shot meat. This value is important in determining the washout period for the interventional study. Adjustments using Fisher exact tests will be utilized to account for any cell counts that are 5 or less.

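### Willingness and compliance are measured over one cycle, so they give only an upper bound on what hunters would accept or complete in the repeated two-year crossover

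*Protocol article*

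**What the plan says.** **What is asked.** In Section 2.5, step 2 (Consent to enrol in study), the coordinator asks each hunter how often they eat lead-shot animals and "if they are willing to abstain from eating lead-shot meat for 9, 18, or 27 days". Those who find the period too long may still join for 9 days or for the longest period they accept. The background evidence is also one-off: preliminary discussions found that "a majority would be willing to abstain from eating wild-shot meat for one month for the study".

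**What is done.** According to the Introduction, "hunters will be asked to abstain from consuming meat harvested with lead projectiles for 7 days" before baseline. They then eat the meal and give blood 2–4 days later. After that, "During the 27 day period, hunters will not consume meat harvested with lead projectiles".

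**What it is used for.** Section 2.7 says that the agree/decline variables "will be used to determine the feasible length of abstaining from eating wild-shot meat", and calls this value important for the washout of the interventional study. Section 2.1 makes the choice of washout part of the primary objective. Its secondary objective is the feasibility of the blinded controlled trial, to be judged by how well participants comply here.

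**What it is meant to inform.** The Introduction describes the later trial as washout, baseline, meal and blood draw. It continues: "Hunters would then repeat this process for a replication of 3 times during the year". After a year the hunter changes projectile and goes through everything again. The Discussion describes the same trial, but ties the three or more yearly occasions to the meal and blood draw and does not say that the washout is repeated.

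**The concern.** A hunter who agrees to one abstention of 27 days has not agreed to several of them over two years. Likewise, compliance through a single cycle does not show that the same person would keep to a schedule of repeated cycles. The plan nevertheless takes the one-off answers as the feasible abstention length and one-cycle compliance as the test of whether the crossover can be run. The article describes no question, measure or adjustment that refers to the repeated schedule.

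The study could therefore recommend a washout that most hunters accept once but fewer accept repeatedly, and report the crossover as feasible on evidence about a lighter commitment. This bears on the secondary objective and on the willingness part of the primary one. It does not touch the blood lead analysis.

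**Working it through.** The documents give no figure for repeated abstention, so there is none to reproduce. The one checkable figure in Section 2.6 does reproduce: a two-sided paired t-test with difference 0.074, SD 0.19, alpha 0.05 and power 0.80 needs n = 54 (power 0.802). This point does not depend on it.

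**1. Burden per hunter in the feasibility study.** Inputs: 9, 18 or 27 days after the meal (Section 2.5) and a 7-day run-in (Introduction).
- Abstention asked about: 9, 18 or 27 days.
- With the run-in: 9 + 7 = 16, 18 + 7 = 25, 27 + 7 = 34 days.

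**2. Burden in the crossover as the Introduction describes it.** Inputs: 3 cycles a year, two years.
- Cycles: 3 × 2 = 6.
- Abstention days: 6 × 9 = 54, 6 × 18 = 108, 6 × 27 = 162.
- Ratio to the abstention asked about: 6.
- Ratio to the total with the run-in: 54/16 = 3.4, 108/25 = 4.3, 162/34 = 4.8.

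**3. Other readings, at 27 days.**

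| Reading | Washouts | Abstention days |
|---|---|---|
| Introduction, three cycles a year | 6 | 162 |
| Introduction, three repeats after the first, each year | (1 + 3) × 2 = 8 | 216 |
| Introduction, counting only the lead-projectile year | 3 | 3 × 27 = 81 |
| Discussion, one washout per period | 2 | 54 |
| Discussion, one washout in all | 1 | 27 |

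On the last reading the abstention equals the one asked about. What still differs is the length of commitment: two years with at least 3 × 2 = 6 meal-and-draw rounds, against one meal here.

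**4. Direction.** Completing k cycles requires completing the first, so the share completing all k cannot exceed the share completing one. In the same way, a hunter who refuses a length once would not be expected to accept it several times. One-cycle figures are thus an upper bound, provided that the crossover recruits similar hunters on similar terms.

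**5. Size.** The gap depends on the loss per cycle and on how losses cluster, and the documents give neither. As an illustration only, assume a constant loss p per cycle, independent across six cycles, so that completion is (1 − p)^6:
- p = 5%: 0.95^6 = 74%
- p = 10%: 0.90^6 = 53%
- p = 15%: 0.85^6 = 38%

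If instead all losses fell in the first cycle, completion would equal one-cycle retention and there would be no gap. So the direction is known and the amount is not.

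**The case against.** **The number of washouts is uncertain.** The Discussion can be read as one starting washout, and the Introduction also calls the washout initial. This stands: six is the plainest reading of the Introduction, not a settled figure.

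**The lead-free year is lighter.** Hunters using lead-free projectiles would not be harvesting lead-shot meat, so abstaining from it should cost them less. This also stands, and a plain sixfold count probably overstates the burden.

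**A feasibility study need not rehearse a two-year trial.** True. The crossover is only proposed, and Section 2.7 calls the abstention value important, not decisive. A length refused even once is useful screening information. But informing that crossover is this study's stated purpose, so its proposed schedule is the right yardstick for what may be concluded.

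**The article condenses the interview.** The call is summarised briefly and the consent form is not shown, so a wider question may exist. Even so, Sections 2.1 and 2.7 state which data settle the matter, and as described those data cover one cycle.

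**A stronger reading is tempting.** A reader might take "We expect 25% attrition from the study" as a loss per cycle, compute 0.75^6 = 18%, and infer that the crossover would lose most of its complete pairs. The documents do not support this:
- The 25% is expected attrition over the whole feasibility study, used in Section 2.6 only to reach the 68 recruits. Nothing carries it to the crossover.
- Independence across cycles is an added assumption.
- A within-hunter contrast needs usable data in each period, not all six cycles. Section 2.8 plans a random-intercept longitudinal model like the one that Section 2.7 describes as able to handle unbalanced data. Missing replicates would cost precision without removing the hunter.

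**Conclusion.** The concern holds as a limit on inference. Willingness and compliance are measured over one cycle, and Sections 2.1 and 2.7 apply them to a crossover that the Introduction describes as about six cycles over two years. At 27 days per washout that is 162 abstention days against 27 asked about, or 34 with the run-in. On the lightest reading of the Discussion the abstention days do not differ, and only the two-year commitment with at least six meals and draws does.

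One-cycle acceptance and retention are therefore upper bounds for the crossover, assuming similar hunters and terms. The documents do not fix how far the true values lie below them. Neither a particular completion rate nor a failed crossover can be inferred.

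**What to change.** 1. Reconcile the Introduction and the Discussion on whether the washout is repeated within each year, so that the burden put to hunters is the planned one.
2. On the existing enrolment call, also ask every hunter, including those who decline, whether they would accept each abstention length (9, 18 or 27 days) on the full planned repeated schedule.
3. In Section 2.7, report that answer beside the one-off answer and observed compliance when choosing the feasible length. It should supplement them, not replace them.
4. State in Section 2.1 that compliance in this study shows the feasibility of a single cycle only.

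The cost is one question on a call already planned, one extra tabulation and some rewording. The question should be in place before recruitment, since decliners are hard to reach after the call. The downside is that stated willingness about a hypothetical two-year schedule is softer evidence than observed behaviour, and the feasibility result may look less favourable.

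### Section 2.6 claims 54 data points in each abstention cohort, but its own attrition leaves 51, and the short-abstention option in Section 2.5 lowers the 18- and 27-day counts further by an unstated, self-selected amount

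*Protocol article*

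**What the plan says.** Section 2.6 sizes the feasibility study with a paired test ("A two-tailed dependent *t*-test was utilized to perform a power analysis") and concludes: "This calculation resulted in a sample size calculation of 54 data points in each abstention cohort". It then expects 25% attrition and sets total recruitment at 68.

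Section 2.5, step 3, takes the blood samples at 9, 18 and 27 days from the same participants. The 68 recruits must therefore supply the stated number at every draw.

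Section 2.5, step 2, reports from preliminary discussions that "a majority would be willing to abstain from eating wild-shot meat for one month for the study". For those who decline because of the length, "they will be offered to still participate and abstain from eating lead-shot meat for 9 days (or the maximum they are willing to abstain". The same telephone call asks how often per week the hunter eats lead-shot animals and whether they would abstain for 9, 18 or 27 days.

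Section 2.7 names projectile group, time and their interaction as predictors, with a random intercept, and says that "this approach can handle unbalanced data (missing data at various time points"). Exposure to lead ammunition and isotope analysis are mentioned as possible further factors. Neither usual intake nor agreed abstention length is named. Section 2.9 relies on REML for missing data.

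**The concern.** A hunter enrolled for 9 days has, by agreement, no abstention sample at 18 or 27 days. One whose own maximum lies between 18 and 27 days has none at 27. This is a planned absence, and Section 2.6 has no term for it. The 25% is already too large for 68 recruits to deliver 54, so there is no slack to absorb it.

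The absence also depends on the hunter's own willingness to abstain. If that willingness is related to how blood lead changes over time, the 18- and 27-day means come from a selected group.

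Both matters bear on the primary objective in Section 2.1, which is to set the washout period and sample size of the interventional trial. Section 3 derives these from the 9-, 18- and 27-day levels, and the longer washouts would rest on the fewest and most selected observations.

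**Working it through.** **Inputs.** From Section 2.6: "Expected Difference in Means: 0.074"; "Expected Standard Deviation: 0.19"; "Desired Power: 0.8"; two-sided alpha 0.05; 25% attrition; 68 recruits. The share *w* of enrolees who accept the full 27 days is not given, so it is an assumption here, ranging from 51% to 100%.

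**1. Reproduce 54.** Read 0.19 as the SD of the paired difference. Then d = 0.074 / 0.19 = 0.389. Exact noncentral-t power for a two-sided paired t-test is 0.795 at n = 53 and 0.802 at n = 54. The stated 54 is reproduced.

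**2. Reproduce 68.** 54 x 1.25 = 67.5, rounded up to 68. To keep 54 after losing 25%, the figure would be 54 / (1 - 0.25) = 72.

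**3. What 68 leaves.** 68 x 0.75 = 51, with power 0.78 for the planned contrast. To keep 54 at a draw, at most 68 - 54 = 14 may be lost for any reason. That is 14 / 68 = 20.6%, below the plan's own 25%.

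**4. Add the short-abstention option.** If the 25% attrition is separate from agreed early stopping, the expected number at day 27 is 68 x 0.75 x *w* = 51*w*:

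| Assumed *w* | 51*w* | Whole samples | Paired-t power at d = 0.389 |
|---|---|---|---|
| 100% | 51.0 | 51 | 0.78 |
| 90% | 45.9 | 45 | 0.72 |
| 80% | 40.8 | 40 | 0.67 |
| 70% | 35.7 | 35 | 0.61 |
| 51% | 26.0 | 26 | 0.48 |

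The day-18 count lies between the day-9 and day-27 counts, depending on how many hunters stop before day 18.

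**5. When the power column applies.** Section 2.6 ties the 0.074 difference to a 7-day washout. The last column therefore holds only if the same difference and SD also describe the day-27 contrast, which the document does not say. The counts do not depend on this.

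**6. If agreed early stopping is inside the 25%.** The day-27 count is then 51 without further reduction, still below 54.

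**The case against.** **The power loss.** A reader might infer that power at day 27 falls to between 48% and 72%. The document does not support this as a general statement. If 0.074 is a decline over 7 days, then with the 28- to 36-day half-life in the Introduction and simple first-order decline, the day-27 decline is (1 - 2^(-27/28)) / (1 - 2^(-7/28)) = 3.1 times as large, or 3.2 times with 36 days. That is about 0.23 to 0.24, and 26 pairs would give power above 99% at SD 0.19. If 0.074 is instead the post-meal level against the baseline taken after 7 days of abstention, short abstainers supply both samples and the option removes no pairs. The planned mixed model also uses partial records. This part of the objection stands. The shortfall in numbers is established; the power figures are conditional.

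**The assumed shares.** The only evidence on acceptance concerns hunters in preliminary discussions, not enrolees. The document does not say whether agreed early stopping is part of the 25%, nor expressly that short abstainers count toward the 68. This also stands, so the size of the further loss cannot be derived.

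**Bias.** A reader might infer that the 27-day mean describes lighter eaters. No section says that frequent eaters refuse long abstention. REML with a random intercept also draws on each hunter's baseline, 2–4 day and 9-day values, and is valid if missingness depends only on observed data or modelled covariates. What remains is a risk, because intake and willingness are recorded but not named in the model.

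**Purpose.** The option is deliberate and may bring in hunters who would otherwise be lost. Section 2.7 uses refusals to judge the feasible length of abstention, so unequal numbers are partly the result sought. That is a good reason to keep the option, but it does not make 54 per cohort correct.

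**Conclusion.** The point holds as a mismatch between Sections 2.5 and 2.6. On the plan's own figures 51 samples are expected where 54 are claimed, if the 25% applies at each draw, as the single figure for every cohort implies. If losses build up over time, 51 is the figure for the last draw and earlier draws have somewhat more.

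It would be wrong to conclude that 54 is right for day 9 and fails only later. The error in the attrition step (multiplying by 1.25) is separate from the short-abstention option and affects every draw.

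The option lowers the 18- and 27-day counts further, provided short abstainers count toward the 68 and lie outside the 25%. Day-27 counts of about 45 to 26 rest on assumed acceptance of 90% to 51%. Selection by willingness is a plausible threat to the later means, and to the washout and sample size taken from them, but its direction and size are unknown.

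**What to change.** **Sections 2.5 and 2.6.** Drop the claim of 54 in each cohort. State the expected number of samples, with precision or power, separately for days 9, 18 and 27: about 51 at day 9 and fewer later. Say whether agreed early stopping is inside the 25% and whether short abstainers count toward the 68. If power is quoted for days 18 and 27, state the difference and SD assumed for each.

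**Section 2.7.** Add the weekly number of lead-shot meals, already asked at the enrolment call, and its interaction with time. Report a sensitivity analysis of the time course restricted to hunters who agreed to 27 days. An interaction of agreed length with time is not a substitute: hunters who agreed to 9 days have no abstention samples at 18 or 27 days. Those terms cannot be estimated with categorical time and rest on extrapolation with linear time.

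**Cost.** Less favourable stated figures and a little more analysis. No new data collection and no extra enrolment.

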### Ethics and dissemination

2.10

All data will be collected and managed by the clinical study coordinator. The data will be kept in a password protected database and a key to participant identifying information will be kept in a separate password protected file.

Blood draws will be collected by an independent contract clinical laboratory (MedLab). Blood samples will be analyzed for lead and complete blood count will be performed by the contract laboratory. Those blood data and time of the blood draw will be kept in the anonymized database. If requested by participants, their lead levels will be shared with them. In the event that the participant lead levels exceed 10 μg/dl (the standard level of concern in Australia and New Zealand) participants will be notified immediately with the recommendation to contact their general practitioner. These participants will not be withdrawn from the study.

Consent forms will be maintained in an alternate password-protected database with identifying information. Photographs of the animal harvested will be maintained in the anonymized database. All consented participants will be texted weekly and called monthly to determine if they have had a meal of harvested meat that week and if they have reported for the blood draw. Participant confidentiality will be maintained through a password protected database with a separate key to identify the anonymized data. Records of the study will be retained for 10 years and anonymized data will be deposited in a publicly-available repository.

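### The 7-day run-in before baseline is missing from the Section 2.5 procedures, and nothing extends abstention to the study meal or limits the baseline-to-meal interval

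*Protocol article*

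**What the plan says.** The protocol article describes the baseline in two ways.

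- **Introduction.** "For this feasibility study, hunters will be asked to abstain from consuming meat harvested with lead projectiles for 7 days", and then: "After 7 days, hunters will provide a baseline blood sample". The study meal follows, then a draw 2–4 days later and draws at 9, 18 and 27 days. Lead-shot meat is again excluded during the 27-day period.
- **Section 2.6.** On the difference of 0.074: "The expected mean difference is derived from preclinical data [17] and 7 day washout".
- **Fig. 5 legend.** A washout comes before the baseline measurement.
- **Section 2.5, step 3.** The baseline rule is: "Prior to the first meat being eaten from the lead-shot animal, a baseline blood lead level will be measured". No abstention is attached to it. The post-meal draw is then triggered by an event with no date: "When a meal is eaten from the harvested game that involves ≥85 g" of mince per person.
- **Section 2.5, step 2.** Candidates are asked how often per week they eat lead-shot animals and "if they are willing to abstain from eating lead-shot meat for 9, 18, or 27 days". The 7-day run-in is not part of the question.
- **Section 2.10.** Consented participants are "texted weekly and called monthly to determine if they have had a meal of harvested meat that week", and the time of each blood draw is kept.
- **Section 2.7.** Baseline is one of the five time points in the repeated-measures model.

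**The concern.** Step 3 of Section 2.5 ties the baseline to one particular animal. A hunter with older lead-shot stock in the freezer could eat from it the night before the draw and still comply with that step. Only the Introduction rules this out, and the step-by-step procedures do not repeat it.

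The larger gap lies after the draw. The stated abstentions cover two stretches: the 7 days before baseline and the 27-day follow-up. Neither covers the time between baseline and the qualifying mince meal, which takes place when the hunter chooses. In that time lead-shot meat from other animals is not excluded, nor are steaks or other non-mince cuts from the study animal itself.

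At stake is the meaning of the change from baseline to the 2–4 day draw. It is meant to show what one meal does after a run-in. With an open interval it also contains whatever was eaten in the gap, less whatever earlier lead decayed in the gap. Both vary from hunter to hunter. A random intercept does not remove this, because it is a change within the person.

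**Working it through.** **Inputs.** Blood half-life h = 28 to 36 days (Introduction). Expected difference 0.074, SD 0.19, two-sided alpha 0.05, power 0.80, paired t-test (Section 2.6; no unit is given for 0.074). Post-meal draw 2–4 days after the meal (Section 2.5). Gap length and interim intake are not given, so the values below are assumptions.

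**The plan's own figure.** A two-sided paired t-test with the noncentral t distribution, difference 0.074 and SD of differences 0.19, gives n = 54 with power 0.802. The stated 54 is reproduced.

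**Decay model.** First-order, with fraction remaining after t days = 0.5^(t/h).

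1. *What 7 days clears.* 0.5^(7/28) = 0.841 and 0.5^(7/36) = 0.874. So 13–16% of an earlier meal's blood lead is gone after the run-in.

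2. *Interim meals raise the change.* Assume no earlier lead, and equal lead-shot meals 7, 14 and 21 days before the study meal, all after the baseline draw.
   - h = 28: 1 + 0.841 + 0.707 + 0.595 = 3.14
   - h = 36: 1 + 0.874 + 0.764 + 0.667 = 3.31

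   The measured rise is about 3.1–3.3 times the one-meal rise.

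3. *Decay lowers the change.* Assume full abstention and 28 days between the two draws. The fall in earlier lead is 1 − 0.5^(28/28) = 50% or 1 − 0.5^(28/36) = 41.7%.

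4. *Run-in versus interval.* Assume each meal raises blood lead by 0.074 at day 3, one equal earlier meal was eaten L days before baseline, and the post-meal draw is G days after baseline. Then the observed change = 0.074 − 0.074 × 0.5^((L−3)/h) × (1 − 0.5^(G/h)).

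| G (days) | L = 3 | L = 7 |
|---|---|---|
| 5 | 0.065–0.067 | 0.066–0.068 |
| 17 | 0.049–0.053 | 0.051–0.055 |
| 31 | 0.034–0.041 | 0.038–0.043 |

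Down a column the change falls by roughly 40–50%. Across a row it moves by at most about 0.004. The open interval matters far more than the missing 7 days.

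5. *Power, if 0.074 is read as the baseline to post-meal difference and the SD stays at 0.19.* At n = 54, power is 0.715 at 90% of 0.074, 0.503 at 70% and 0.290 at 50%.

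**The case against.** Several points on the other side stand.

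- **The 7-day rule is in the plan.** The Introduction states it for this study, and both baseline conditions can be met together. A reader might infer from Section 2.5 that the run-in is not applied at all. The article does not support that: the two places need reconciling, and the rule is not absent.
- **Restoring the 7 days alone changes little.** It clears only 13–16% at the stated half-lives, as the table shows.
- **The contact schedule gives no gap length.** A reader might take the monthly calls in Section 2.10 as a sign that waits of weeks to months are expected. They are routine contact with every consented participant, including those in follow-up.
- **Part of the exposure is recorded.** Draw times are kept, the study meal is texted in, and weekly texts ask about harvested-meat meals. It would be wrong to say that interim exposure goes unrecorded. What is missing is a stated use of these records. Section 2.7 says only that exposure to lead ammunition may be included as a factor. Section 2.9 says REML handles mistimed measurements, but that does not account for meals eaten in between.
- **The link to the primary objective is partial.** Section 2.1 describes post-meal levels against levels after abstention, and Section 2.6 does not say which contrast 0.074 represents. The power figures are therefore conditional.
- **The scenarios are chosen, and they pull in opposite directions.** A reader might infer that decay could cancel the effect. That would need a residual from earlier meals of 0.074/0.50 = 0.148 to 0.074/0.417 = 0.178, and the article gives no such level.

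The argument that an article condenses such detail has some weight for the length of a visit window. It has less for the rest. Section 2.5 goes down to photograph resolution and postage, states its own baseline rule, and that rule is looser than the one in the Introduction.

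**Conclusion.** The point holds as an inconsistency plus an open interval. Section 2.5 and the enrolment question do not carry the run-in that the Introduction requires and that Section 2.6 and the Fig. 5 legend rely on. No section extends abstention across the baseline-to-meal interval or limits its length. A participant who follows the plan as written can therefore give a baseline to 2–4 day change that is not the effect of one meal.

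Neither the net size nor the direction can be stated, because the article gives no gap lengths or intakes. The figures of 3.1–3.3 times and 42–50% show what the stated half-lives imply under assumed gaps and first-order decay. They are not estimates of bias in this study. The sample size of 54 reproduces and is not changed by this point. It is a worthwhile, cheap improvement rather than a required correction.

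**What to change.** - In Section 2.5, step 3, carry over the Introduction's run-in as a condition for the baseline draw, so that both sections give one rule.
- State that abstention from all lead-shot meat, including other cuts of the study animal, continues from the run-in through baseline until the study meal.
- State a maximum baseline-to-meal interval. Its length is for the investigators to choose.
- In step 2, ask about the whole abstention, including the run-in and the wait for the meal, as well as the 9, 18 or 27 days.
- Record the date of the last lead-shot meal before each draw, and say in Section 2.7 that the interval and any interim meals can enter the model.

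The cost is wording, a few extra texts and slightly more burden on hunters. A repeat baseline draw when the interval is exceeded is optional and not needed for the fix. No stated sample size changes.
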